### Plans to give access to the full protocol, participant level-data, and statistical code {31c}

There are no plans to give access to the full protocol, participant level-data, or statistical code before sponsor received CE-mark for the investigational device. After investigational device got the CE-mark to be distributed on the European market, the study results will be published in a scientific journal. Then the datasets the clinical study and statistical code will be available from the corresponding author on reasonable request, as is the full protocol.

## Oversight and monitoring

### Composition of the coordinating center and trial steering committee {5d}

No Data Safety Monitoring Board has been appointed for this study. Since the investigational device and the comparator only differ in the silver coating, no additional SAEs are expected because of study treatment compared to standard treatment with the approved comparator. The blood samples for silver analysis will only be analyzed after data base lock, therefore, potential high silver concentrations in the serum could not be identified during the clinical trial. If a SAE is reported via the eCRF, a medical monitor will be alarmed and assess the SAE be severity and relationship to treatment.

The sponsor and the coordinating investigator will have biweekly telephone conferences to discuss the current events. Each primary investigator at each study site is responsible for the local organization of the trial, including recruitment, taking informed consent and collection of data. At every monitoring visit, the clinical research associate will try to discuss with at least one of the site investigators about the current events and inform the sponsor about the results of this discussion.

### Composition of the data monitoring committee, its role and reporting structure {21a}

Due to the low risk profile of the investigational product and the long experience with silver application for medical purposes no Data Safety Monitoring Board will be appointed for the study.

### Adverse event reporting and harms {22}

All adverse events and device deficiencies mentioned by the patient or observed by an investigator will be reported together with the causality via the eCRF. A list of predefined AADEs, crucial for the primary endpoint, is presented in the clinical investigation plan. SAEs will be reported according to the applicable regulations.

### Frequency and plans for auditing trial conduct {23}

The clinical data and conduct will be monitored by trained clinical research associates employed by the contract research organization. One hundred percent of the data will be monitored. First monitoring visit at a study site will be planned shortly after the first implantation. Following monitoring visits will be conducted according to the enrollment speed of the study site.

### Plans for communicating important protocol amendments to relevant parties (e.g., trial participants, ethical committees) {25}

All substantial amendments, as defined by the Medical Device Coordination Group [22], will be submitted to the ethics committee and the competent authority. Non-substantial amendments will be notified to the ethics committee and the competent authority. If an amendment concerns or affects patients in any way, they will be informed about the changes and if necessary, consent will be requested again.

### Dissemination plans {31a}

Both positive and negative results will be reported in international peer-reviewed journals.

## Discussion

### Selection of indication

The non-inferiority aspect of the clinical trial could be shown with any fracture of a patient, but as distal tibia fractures show by far the highest infection rate, this is the most appropriate indication for our study to show a potential clinical benefit for the patient in terms of improvement of infection prophylaxis by reduction of infection rated in the coated vs. the uncoated group.

### Radiological assessment (X-ray) — fracture healing

During the follow-up visit at weeks 1 and 6 and after 3-, 6-, and 12-month imaging assessment will be conducted. At each follow-up visit, images are reviewed to determine fracture healing:Callus bridging on three of four cortices on orthogonal radiographsNo bridging callus on three of four cortices on orthogonal radiographsSigns of Malunion defined as more than 10 mm of shortening and more than 5 degrees of angulation in any plane

Based on these assessments fracture healing will be defined for each subject as:Complete healing is defined as bridging callus on three of four cortices on orthogonal radiographs within 6 months after implantation.Delayed Union is defined as failure to show bridging callus on three of four cortices on orthogonal radiographs after 6–9 months.Non-union is defined as failure to show bridging callus on three of four cortices on orthogonal radiographs after 12-month FU.Signs of malunion defined as more than 10 mm of shortening and more than 5 degrees of angulation in any plane after 12-month FU.

The last assessment for each subject will be considered for the secondary endpoint.

In order to get an independent assessment of the radiographic images, an independent adjudication board will be formed consisting of radiologists which are not participating in the clinical trial. All images will be sent to the independent adjudication board at the end of the study, where the images will be evaluated for healing.

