#### Follow-up Visits

At the five follow-up (FU) visits of up to a year the patient will be accompanied in his or her healing process and all assessments for the defined endpoints will be made. The point of study termination is defined as the date of 12-month FU for patients with regular study termination. Following completion of the 12-month FU visit, the subject will be treated according to the standard of care practice of the treating surgeon.

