### Participant timeline {13}

The participant timeline is shown in Table 2.

**Table 2 Tab2:** Study schedule. Assessment windows will be as follows: screening/enrollment visit (day −21 to day 0), implantation (day 0), 1-week FU visit (7 ± 3 days), 6-week FU (42 ± 7 days), 3-month FU (90 ± 14 days), 6-month FU (182 ± 14 days), 12-month FU (365 ± 30 days)

Investigations	Enrollment	Implantation	1-week	6-week	3-month	6-month	12-month
Informed consent	X						
Randomization		X					
Implantation		X					
Adverse event reporting	X	X	X	X	X	X	X
Local Argyria	X		X	X	X	X	X
Assessment of Infection	X	X	X	X	X	X	X
Blood serum (silver levels)	X	X	X	X	X	X	X
Wound fluid (silver levels)		X					
Radiological assessment (X-ray)	X		X	X	X	X	X
AOFAS score	X		X	X	X	X	X
Questionnaires: VAS (pain), DRI, EQ-5D-5L	X		X	X	X	X	X
Assessment of weight bearing	X		X	X	X	X	X

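### The rule that the last film decides the fracture-healing endpoint conflicts with the 6-month limit on complete healing, and the delayed-union category does not fit the imaging schedule

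*Protocol article*

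**What the plan says.** *Outcomes {12}* names as a secondary outcome the comparison between arms of the rate of completely healed subjects, judged by local and central readers. The states are defined in the Discussion, under *Radiological assessment (X-ray) — fracture healing*:

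- Healed: "Complete healing is defined as bridging callus on three of four cortices on orthogonal radiographs within 6 months after implantation".
- Delayed union: "Delayed Union is defined as failure to show bridging callus on three of four cortices on orthogonal radiographs after 6–9 months".
- Non-union: "Non-union is defined as failure to show bridging callus on three of four cortices on orthogonal radiographs after 12-month FU".
- Then, for the endpoint: "The last assessment for each subject will be considered for the secondary endpoint".

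The same section fixes the imaging: "During the follow-up visit at weeks 1 and 6 and after 3-, 6-, and 12-month imaging assessment will be conducted". Table 2 (*Participant timeline {13}*) puts the 6-month visit at 182 ± 14 days and the 12-month visit at 365 ± 30 days. *Follow-up Visits* ends the study there: "The point of study termination is defined as the date of 12-month FU for patients with regular study termination".

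**The concern.** Complete healing is a statement about the first six months. The last film of a completer is taken about a year after surgery. One sentence therefore makes the endpoint time to bridging, cut at six months, and the other makes it status at the end of follow-up. These are different questions, and late-healing fractures are counted differently by each.

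Three further problems follow from the same text. For an early leaver, the last assessment may be a film from the first weeks, when an unbridged fracture is expected and says nothing about failure. Delayed union is tied to an interval in which no visit is planned. The failure categories also overlap.

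If this is left open, the reported healed rate depends on which sentence the analyst follows. That choice should not be made after the results are known.

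**Working it through.** The plan attaches no figure to the healing definitions, so there is none to reproduce. The check is date arithmetic on Table 2, followed by a comparison of the rules.

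**1. Imaging windows (Table 2), in days after implantation**

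- Week 1: 7 ± 3 = 4–10
- Week 6: 42 ± 7 = 35–49
- Month 3: 90 ± 14 = 76–104
- Month 6: 182 ± 14 = 168–196
- Month 12: 365 ± 30 = 335–395

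**2. Time limits in the definitions, converted to days**

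- 6 months: 6 × 365.25/12 = 182.6, about day 183
- 9 months: 9 × 365.25/12 = 273.9, about day 274

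**3. Last film against the healing limit.** A completer's last film is on day 335 at the earliest, and 335 > 183. Taken literally, that film alone can never show that bridging happened within six months. Taken as bridged at the last film, the six-month limit has no effect.

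**4. Delayed union against the schedule.** No film is scheduled on days 197–334. On a calendar-day reading, only days 183–196 of the 6-month window lie in the 6–9-month interval. No visit is dedicated to it.

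**5. The rules side by side**

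| Month-6 film | Month-12 film | Six-month definition | Bridged at last film | Failure definitions met |
|---|---|---|---|---|
| bridged | bridged | completely healed | healed | none |
| unbridged | bridged | not completely healed | healed | delayed union, if the month-6 film counts for 6–9 months |
| unbridged | unbridged | not completely healed | not healed | delayed union and non-union, no precedence stated |
| none (left unbridged after week 1 or 6) | none | cannot be determined | unbridged | neither could have been observed |

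Row 2 is the direct conflict. Row 3 is the overlap. Row 4 is the early leaver.

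**6. Size of row 2.** Let h6 and h12 be the proportions bridged by months 6 and 12. The share whose category depends on the rule is h12 − h6. The document gives neither value, so these are assumptions, applied to the 96 implanted subjects per arm in *Sample size {14}*:

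| h6 | h12 | h12 − h6 | of 96 |
|---|---|---|---|
| 0.60 | 0.90 | 0.300 | 28.8 |
| 0.70 | 0.95 | 0.250 | 24.0 |
| 0.80 | 0.95 | 0.150 | 14.4 |
| 0.90 | 0.963 | 0.063 | 6.0 |

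Table 1 cites 2.5% for delayed healing or union, from an outside source whose definition is not given. At face value that would be 0.025 × 96 = 2.4 per arm. The plausible range is too wide for any single figure to be stated.

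**The case against.** **A serial reading is available.** The article says that each subject's status rests on the assessments made across visits. A reader could take bridging by month 6 as healed, later bridging as delayed, and none by month 12 as non-union. That is sensible, and because of it the text is ambiguous rather than certain to misclassify. But it works only if the last-assessment sentence is set aside, so the conflict stands.

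**Six months may mean the 6-month visit.** Table 2 itself lets that visit run to day 196. Read by visit, bridging seen on days 183–196 is on time. This stands. It is why one should not infer that about half of the subjects seen at that visit are misclassified: such a figure needs a calendar-day cut-off and evenly spread visits, and the article supports neither. The visit-based reading does not cure the clash with the last-assessment sentence, or the overlap of delayed union with non-union.

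**Handling of drop-outs belongs in the analysis plan.** In detail, yes. The article does not say that early leavers count as unhealed. But it does fix which film is used, and for them that film is uninformative.

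**The primary endpoint.** Delayed union and non-union are listed adverse device effects in Table 1, so a reader might infer that the primary composite is misclassified too. The documents do not support that. The last-assessment sentence is limited to the secondary endpoint, complete healing is not in Table 1, and under *Adverse event reporting and harms {22}* events are reported through the eCRF. Nothing says that the radiographic definitions decide those events.

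**Malunion.** A reader might add it to the list: "Signs of malunion defined as more than 10 mm of shortening and more than 5 degrees of angulation in any plane after 12-month FU". It conflicts with neither the schedule nor the last-assessment rule, because the 12-month visit is a scheduled imaging visit and the completer's last. Requiring both criteria is stated consistently, and preferring either one is a matter of choice.

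**Conclusion.** The point holds for the secondary fracture-healing endpoint. Three defects are on the page:

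- The six-month limit and the last-assessment rule give opposite answers for fractures that bridge between the 6- and 12-month films.
- The last-assessment rule uses uninformative early films for subjects who leave in the first weeks.
- Delayed union has no dedicated film and overlaps with non-union.

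The first rests only on Table 2 and the definitions, with no outside assumption. The number of subjects affected cannot be computed from the document. The 6 to 29 of 96 per arm in the table above is an illustration on assumed bridging rates.

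No bias towards either arm is shown: *Who will be blinded {17a}* keeps the subject, the evaluator and the adjudication board blinded, and the same rules apply to both arms. No sample-size figure changes. An effect on the primary composite is an open question for the sponsor to answer.

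**What to change.** Remove the last-assessment sentence and define the states by visit, using the films already scheduled:

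- Healed: bridged at or before the 6-month visit, on any day in its window.
- Delayed union: unbridged at the 6-month visit and bridged at the 12-month visit.
- Non-union: unbridged at the 12-month visit.

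These states do not overlap, so no precedence rule is needed. Where the 6- or 12-month film needed to assign a state is absent, treat the status as missing, not as unhealed. State also whether these radiographic definitions govern the delayed-union and non-union events in the primary composite.

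The cost is wording only: no added visit, film or subject. The downside is that some subjects will have a missing status where a carried-forward one would have been used. The article has the analysis plan finalized before database lock and unmasking, and has the adjudication board read the images at the end of the study, so the change can be made while blinded.

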### Wound fluid

To determine a local concentration of silver ions in the patient’s body close to the implant, a sample of the wound fluid should be collected 24 h and 48 h after implantation, if a drainage has been applied to the patient. To the best of our knowledge, no other clinical trial with this high number of subjects investigated the silver concentration in the wound fluid after the implantation of silver-coated devices.

### Market approval

For market approval of such an antibacterial coating, not only safety but also a clinical benefit by improving infection prophylaxis needs to be shown by clinical data compared to the uncoated comparator device. As the underlying infection rate of the trauma to be treated is extremely important for the calculation of the sample size and feasibility of such a study, the selection of an appropriate injury and indication is essential in this context.

### Trial status

The randomized controlled trial (RCT) recruitment and consequent implantations started in December 2021 and is planned until June 2023. Follow-up will be conducted over 12 months for each patient.

## Data Availability

The datasets used and/or analyzed during the current study will not be made available.

## Abbreviations

AADE: Anticipated Adverse Device Effects
AOFAS: American Orthopaedic Foot and Ankle Score
CRA: Clinical research associate
DRI: Disability Rating Index
eCRF: Electronic Case Report Form
FU: Follow-up
MRI: Magnetic resonance imaging
PEO: Plasma electrolyte oxidation
RCT: Randomized controlled trial
(S)AE: (Serious) Adverse Event
TEAE: Treatment Emergent Adverse Event
VAS: Visual analog scale
